#### 2.7.8 Composite drive score

As in Marcotte et al. (2022), primary variables from various individual components of the drives will be integrated to produce a single value indicative of overall driving performance (or a “Composite Drive Score”). Composite Drive Scores will be calculated for each post-dosing drive and compared to the baseline drive (i.e., prior to cannabis and alcohol dosing) within a given session. In order to calculate the Composite Drive Score, z-scores will be established based on baseline driving performance, using the mean and standard deviation of each score (i.e., the primary and secondary outcomes) for each participant across all seven baseline drives (the baseline Composite Drive Score for each participant will have a mean z-score of 0, with a standard deviation of 1). Higher scores on this measure will indicate worse driving performance. For this study, the Composite Drive Score will be comprised of primary and secondary driving outcomes from the Car-Following Task (e.g., SDLP, Coherence), Divided Attention Task (e.g., SDLP, SDSP, percent correct responding), and crash avoidances (e.g., Reaction Time, Time to Collision).

### 2.8 Computerized cognitive and psychomotor measures

The DRUID application (Impairment Science Inc., Cambridge, MA, United States), which has been shown to be sensitive to both alcohol (Richman and May 2019) and cannabis impairment (Spindle et al., 2021), will be used to measure cognitive and psychomotor performance. The DRUID application includes four 30–45 s tasks that measure reaction time, decision-making, hand-eye coordination, and time estimation under conditions of divided attention in addition to a balancing task. On Task 1, shapes (either a square or circle) flash on the screen; one shape is designated as the target shape and the other the control shape. Participants are asked to touch the screen where the target shape appears and to touch the top of the screen when the control shape appears. Reaction time in touching the screen is assessed along with the number of errors. On Task 2, participants estimate when they feel 30 s have passed by pressing a button on the screen and, while waiting to press the button, they touch the screen where shapes briefly flash. Reaction time to the stimuli and accuracy of time estimation are measured. On Task 3, participants try to keep their finger on a circle that moves randomly around the screen while also counting the number of squares that flash on the screen. For Task 4, participants stand on one leg for 15 s while holding the iPad in their same hand, then following completion, perform this task on the opposite leg (with the iPad in the other hand); DRUID accesses data from an accelerometer located in the iPad to measure stability and balance during this task. Performance data from each of the four tasks is integrated using a statistical algorithm to yield a Global Impairment Score, the primary outcome measure for the DRUID. The DRUID battery will be given at baseline and again at various timepoints up to 7.5 h post-dosing (see Figure 1). The DRUID will be administered immediately after driving.

### 2.9 Standardized field sobriety tests

A battery of field sobriety tests commonly used by law enforcement to assess impairment from drugs/alcohol at the roadside will be administered to participants by research staff. Research staff were formally trained on how to administer these tests alongside active-duty police officers during a three-day in-person instructional course held by the Baltimore County Police department, normally only offered to police personnel. In addition, a retired certified Drug Recognition Expert (DRE) for the Maryland State Police provided supplementary training and will periodically attend study sessions to confirm study staff maintain fidelity to the task procedures. A total of six field sobriety tests are administered: the Horizontal Gaze Nystagmus (HGN), which will include the Vertical Gaze Nystagmus (VGN), the Walk-and-Turn (WAT), the One-Leg Stand (OLS), Lack of Convergence (LOC), the Modified Romberg Balance (MRB), and the Finger-To-Nose (FTN). The HGN, WAT, and OLS are the core battery of tests known as Standardized Field Sobriety Tests (SFSTs) that have been shown to be sensitive to alcohol intoxication (Stuster and Burns, 1998); the remaining tests are also commonly used by law enforcement but are not part of the core SFST battery. While participants perform each test, the task administrator will look for distinctive behavioral indications (i.e., “clues” or “cues”) that may indicate impairment, which will be scored as either present (1) or not present (0); in general, a greater number of clues/cues on a given task suggests a greater likelihood of impairment. Note that the SFST battery includes validated “clues” of impairment while the remaining tests include “cues” of possible impairment that have not been validated *via* formal research.

For the HGN, the task administrator holds a stimulus 12–15 inches from the participant’s face to assess involuntary jerking of the eyes *via* six possible clues: lack of smooth pursuit (left and right eye), distinct and sustained nystagmus at maximum deviation (left and right eye), and onset of nystagmus prior to 45° (left and right eye). Participants are instructed to stand with their feet together, with hands at their sides, hold their head still, and follow the motion of the stimulus with their eyes only. Each eye is checked for each clue, beginning with the participant’s left eye, and all checks are performed twice. Lack of smooth pursuit is performed by passing the stimulus in front of the eyes, from the far tip of each eye to the other (not far enough that the participant would have to move their head), over the course of 2 seconds. The presence of jerking during the smooth passing of the eyes is a clue. Distinct and sustained nystagmus at maximum deviation is performed by passing the stimulus to the far side of the participant’s eye (until little to no white is showing in the corner of the eye at maximum deviation). The presence of jerking at maximum deviation is counted as a clue. Onset of nystagmus prior to 45° is assessed by slowly moving the stimulus from the center starting position to the edge of the participant’s left or right shoulder. The movement should take approximately 4 s and any jerking that occurs prior to 45° is counted as a clue. The presence of four or more of clues on the HGN indicates the individual is impaired (Stuster and Burns, 1998; NHTSA, 2017).

For the VGN, the task administrator holds a stimulus 12–15 inches from the participant’s face, parallel to the floor. The stimulus is raised until the subject’s eyes are as elevated as possible and is then held in place for 4 seconds. The process is repeated twice. The presence of jerking is counted as a clue (Citek et al., 2003).

LOC is assessed by performing two circular motions with the stimulus before approaching the bridge of the participant’s nose. Failure for the eyes to converge (i.e., crossing of the eyes) is considered a cue of possible drug/alcohol impairment. Visual deficits for each participant will be addressed during screening and will be excluded from analyses of the HGN, VGN, and/or LOC task if visual deficits persist. Additionally, for all eye-related measures, prescription eyeglasses will be removed prior to the test.

When administering the HGN, VGN, and LOC, task administrators will use the ToxOptix X3 (ToxOptix, Austin, TX) as the stimulus. This is a specialized pen-shaped tool designed specifically for administering these field sobriety tests. The ToxOptix X3 guides the administrator on proper timing for each individual test *via* a series of vibrations (e.g., the device vibrates to indicate when the administrator should hold the stimulus in place during the HGN). Overall, use of this device can better standardize task administration relative to a conventional stimulus (e.g., a pen).

For the WT, participants are asked to take nine heel-to-toe steps down a straight line (clearly marked on the ground), starting with the right foot. On the ninth step, participants will turn around, pivoting on the left foot using a series of small steps, and take nine heel-to-toe steps back in the opposite direction. There are eight possible clues: failure to balance during the instructional phase, initiating movement prior to instruction, stopping during the task, not touching feet heel-to-toe (a separation distance of 6 inches or greater), stepping off of the line, using their arms for balance, an improper turn, and an incorrect number of steps in either direction. Detection of two or more clues indicates drug/alcohol impairment (Stuster and Burns, 1998; NHTSA, 2018).

For the OLS, participants are asked to raise one foot 6 inches off the ground and count until they are told to stop; they will be stopped by the task administrator after 30 s. There are four possible clues on the OLS: swaying while balancing, using arms for balance, hopping on one leg, and putting their foot down prior to completion. Failure on two or more clues indicates drug/alcohol impairment (Stuster and Burns, 1998; NHTSA 2018).

For the MRB, participants are asked to stand with their feet together and arms at their side, with their eyes closed and head tilted back, and to estimate the passing of 30 s. There are four possible cues of impairment: incorrect time estimation (+/− 5 s), eyelid tremors, body tremors, and swaying.

For the FTN, participants are asked to stand with their feet together and arms at their side, with both index fingers pointed at the ground and their eyes closed and head tilted back. They are then instructed to touch the tip of their index finger to their nose in a specified order. Possible cues of impairment include: failure to follow the instructed order of nose presses and number of failed attempts at touching the tip of their finger to their nose.

The total number of clues/cues of impairment detected will be summed to produce an overall score for each task (our primary outcomes), with higher scores indicating greater impairment; another outcome is the cumulative number of clues/cues of impairment across all tests. Participants are video recorded while performing the field sobriety tests to allow for a second person to score the tests at a later time; agreement between these two coders will be calculated and individual discrepancies between coders will be resolved by a third coder. Eye-related tests are filmed *via* a GoPro mounted on the administrator’s forehead. To further ensure proper technique is followed by task administrators and that clues/cues of impairment were scored correctly, the aforementioned retired DRE who helped train the research staff will score a subset of the recorded tests (approximately 25%, chosen at random). All SFSTs will be given at baseline and at various timepoints after drug administration (up to 7.5 h post-dosing). Each of these tests will be administered immediately after driving.

### 2.10 Subjective drug effects

A modified 25-item Drug Effect Questionnaire (DEQ; Spindle et al., 2018; Spindle et al., 2021) will be administered that includes items assessing: positive (e.g. “like drug” and “pleasant drug effect”) and negative subjective drug effects (e.g. “unpleasant drug effect” and “anxious/nervous”), behavioral/mood states related to acute high Δ9-THC cannabis exposure (e.g. “high”, “paranoid”, and “hungry/have munchies”), and participants’ perceived level of impairment (e.g. “trouble with memory”, “difficulty with routine tasks”, “confidence in driving ability”). Each item will be presented individually on a 100 mm visual analog scale (VAS) with a horizontal line anchored from 0 (“not at all”) on the left to 100 (“extremely”) on the right. The one exception is the question, “Would you drive in your current state,” which requires a yes or no response.

The Subjective High Assessment Scale (SHAS) (Martin et al., 1993) and the Biphasic Alcohol Effects Scale (BAES) (Schuckit, 1980) will be administered to assess alcohol-specific subjective effects. For the SHAS, participants rate alcohol effects on a 100 mm VAS (0 or “not at all” to 100 or “extremely”). Example items include: muddled/confused, slurred speech, dizzy, drunk, distorted sense of time, and difficulty concentrating. Items are summed to produce an overall score (the primary SHAS outcome). The BAES measures stimulant (e.g., energized, excited, stimulated) and sedative (e.g., inactive, sedated, sluggish) effects of alcohol with 14 items. Participants rate each item on a scale from 0 (“not at all”) to 10 (“extremely”). Overall stimulant and sedative scores are calculated from the individual items (two primary BAES outcomes). These questionnaires, along with the DEQ, will be given at baseline and at various timepoints after drug administration (see Figure 1). These questionnaires will be administered immediately before driving.

After each drive, participants will answer two questions to assess their perceived driving performance: “how much did the study drugs affect your driving?” (0 [not at all] to 100 [extremely]) and “how well did you drive?” (0 [not well at all] to 100 [extremely well]).

### 2.11 Physiological measures

Heart rate (HR), systolic blood pressure (SBP), and diastolic blood pressure (DBP) will be measured in the seated position with an automated device at baseline and at regular intervals after drug administration.

### 2.12 Breath alcohol procedure

The Alco-Sensor IV breathalyzer will be used to measure participants’ BAC throughout the sessions. This will be used to ensure that participants reach the target BACs and to monitor BAC levels over time. BAC readings will not be viewable to participants or study staff to maintain dose blinding and will be measured by a nurse who will not administer any of the aforementioned tests.

### 2.13 Blood specimens

Whole blood specimens will be collected using 6 ml gray-top vacutainer tubes and stored frozen at −80°C until sent to a designated laboratory for analysis. Blood collection timepoints for each route of cannabis administration (oral and vaporized) are depicted in Figure 1. Concentrations of Δ9-THC and the two primary metabolites of Δ9-THC (11-OH-Δ9-THC; Δ9-THC-COOH) will be determined using LC-MS/MS.

### 2.14 Data presentation and statistical analysis plan

Power analyses for each primary outcome were conducted in R, using the SIMR package (Green and Macleod, 2016), which estimates power for linear mixed models by fitting a regression model multiple times under different scenarios, or simulations (100 simulations were performed for each power calculation). Effect sizes (Cohen’s d) and data (means and SDs) were obtained from prior alcohol/cannabis co-use studies (Hartman et al., 2016a) and/or prior studies conducted in our laboratory (Spindle et al., 2018; Spindle et al., 2021) that administered the proposed doses of oral/vaporized cannabis or alcohol alone. Overall, all power analyses revealed that 32 participants (16 men/16 women) in Part 1 and Part 2 would provide sufficient power (≥ 0.80 power for all 100 simulations) to test the study hypotheses stated.

For each outcome, descriptive statistics (means and standard deviations) will be generated. Linear mixed models will be used to test for differences across experimental conditions. Hypothesis tests will be two-sided, and significance will be set at *p* < 0.05. Factors entered into these models will include: Time (number of levels will differ depending on outcome variable), Alcohol Dose (0%, 0.05%, and 0.08%), Cannabis Dose (0, 10, and 25 mg Δ9-THC), and Sex (male or female). Time, alcohol dose, and cannabis dose will be within-subject factors (i.e., repeated measures); sex will be a between-subject factor. Maximum concentration (C_max_) and area under the curve (AUC) for Δ9-THC and Δ9-THC metabolites (11-OH-Δ9-THC; Δ9-THC-COOH) will be entered as covariates. Holm-Bonferroni corrections will be used to control for multiple comparisons. Data will be inspected for normality (skewness, kurtosis, outliers) and, where necessary, data transformations will be applied. Missing data is expected to be rare, as tasks and instruments are computerized, and field sobriety tasks will be video recorded. Additionally, if a participant presents elevated concentrations of Δ9-THC or Δ9-THC metabolites at baseline, and these values do not increase following active drug administration, this participant will be excluded from analysis.

For Part 1 and Part 2, a priori planned comparisons will be conducted to compare mean peak change-from-baseline scores for each outcome for: (1) alcohol alone (BAC 0.05%) to alcohol with cannabis (BAC 0.05% + 10 mg Δ9-THC and 25 mg Δ9-THC); and 2) cannabis alone (10 mg Δ9-THC and 25 mg Δ9-THC) to cannabis with alcohol (BAC 0.05% + 10 mg Δ9-THC and 25 mg Δ9-THC). Additionally, planned comparisons will compare impairment (e.g., DRUID scores, composite drive scores) between cannabis with alcohol (BAC 0.05% + 10 m g Δ9-THC and 25 mg Δ9-THC) to the positive control condition (alcohol alone: BAC 0.08%). Correlations will be conducted to assess the relations between DRUID and driving performance. Sensitivity and specificity analyses will be conducted to characterize the effectiveness of the DRUID for determining driving impairment. Specifically, we will plot the sensitivity (true positive rate) and specificity (true negative rate) of the DRUID at identifying impaired driving by comparing various DRUID cutoffs to established cutoffs for driving simulator data that are indicative of clinically meaningful impaired driving in real-world settings (e.g., SDLP change-from-placebo ≥ 2.4 cm; Jongen et al., 2016). Sensitivity and specificity will be calculated as follows: sensitivity (100 × [TP/(TP + FN)]) and specificity (100 × [TN/(TN + FP)]).

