
## 1 Introduction

Cannabis (marijuana) and alcohol are two of the most used drugs of abuse in the world. In U.S. surveys conducted in 2019, approximately 48 million adults reported use of cannabis (Substance Abuse and Mental Health Services Administration, SAMHSA, 2021), and alcohol was used by approximately 140 million U.S. adults (SAMHSA, 2021). Alcohol use has a severe toll on public health; 28% of all fatal automobile accidents involve culpable drivers determined to have been under the influence of alcohol at the time of crash (National Highway Traffic Safety Administration, NHTSA, 2018). Like alcohol, cannabis that contains delta-9-tetrahydrocannabinol (Δ9-THC) can impair driving performance by disrupting psychomotor skills, cognitive abilities, and attention (Sewell et al., 2009; Spindle et al., 2018; Arkell et al., 2020), and detection of Δ9-THC concentrations in blood indicative of recent cannabis use is associated with a significant increase in crash risk (Preuss et al., 2021).

Coincident with increased cannabis legalization for medicinal and/or non-medicinal (“recreational”) purposes, there has been an increase in the incidence of driving under the influence of cannabis, (DUIC; Kelley-Baker et al., 2017). Increases in DUIC are likely due to decreased harm perceptions associated with cannabis use (Berg et al., 2015) as well as increased access to high Δ9-THC cannabis, which is steadily increasing in potency each year (Chandra et al., 2019). Of particular concern, an increasing number of people report regularly using alcohol and cannabis concurrently (i.e., “co-use”), most often in states where cannabis is legal (Kim et al., 2020), and many of these individuals report driving following alcohol-cannabis co-use (Fink et al., 2020). Importantly, when administered together, alcohol and cannabis produce additive or synergistic impairment (Sewell et al., 2009; Hartman et al., 2015; Yurasek et al., 2017), which is likely driven, in part, by pharmacokinetic interactions between alcohol and Δ9-THC (Hartman et al., 2016b). Individuals who have ingested both alcohol and cannabis also have a greater probability of being involved in a car accident and are more likely to be culpable for the accident than individuals who have ingested only alcohol or cannabis (Drummer et al., 2020).

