The planned studies described here will extend prior alcohol/cannabis co-use studies by characterizing impairment associated with the co-use of alcohol and cannabis consumed orally or *via* vaporization. To date, no studies have characterized the effects of co-using alcohol and cannabis edibles, and only one study examined co-use of alcohol and vaporized cannabis. In the lone published study that evaluated the combined effects of alcohol (blood alcohol concentration, BAC, of 0.065%) and vaporized cannabis (14.5 mg and 33.5 mg Δ9-THC), the two drugs displayed additive effects on driving impairment; the increased impairment under co-use conditions was seemingly mediated by pharmacokinetic interactions between alcohol and cannabis (i.e., increased plasma Δ9-THC and 11-OH-Δ9-THC concentrations under co-use vs. cannabis-only conditions; Hartman et al., 2015). The present research will build on prior co-use studies with smoked cannabis to advance knowledge by dosing participants with alcohol doses targeting BACs that define legal intoxication in Europe (0.05% both alone and with cannabis) and most U.S. states (0.08% alone), administering multiple Δ9-THC doses (10 and 25 mg) that facilitate analysis using the standard Δ9-THC dosing unit (5mg; Volkow and Weiss, 2020), and enrolling an equal number of men and women to explore possible sex differences on study outcomes.

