
The primary aim of this two-part study is to characterize subjective, cognitive and psychomotor, and driving impairment from oral and vaporized high Δ9-THC cannabis, when administered alone and in combination with alcohol. A secondary aim is to explore possible pharmacokinetic interactions between alcohol and oral/vaporized cannabis. A key aspect of this protocol was the development of custom simulated driving scenarios designed to test important aspects of driving performance that are known to be impacted by alcohol and cannabis exposure. By incorporating different tasks and scenarios that have been independently found to be sensitive to alcohol and cannabis effects, this custom simulation can provide a holistic view of how these substances impact driving performance when taken alone and together. To promote greater standardization and future cross-study comparisons among simulated driving studies, we describe the characteristics of the custom drive scenarios and provide a copy of the simulated drives along with an R script to extract and organize the data (available for download at https://github.com/[name]/STISIM_impaired_driving). Below we also describe the study procedures and specific outcome measures, detail our statistical analysis plan, and conclude by commenting on the implications that this research can have for public safety as well as policy and regulatory decisions for alcohol and cannabis.

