## 3 Comments

Controlled human laboratory studies are a valuable method for developing a detailed understanding of the acute impairment profile of alcohol, cannabis, and co-use of both substances. However, studies on alcohol and cannabis co-use are scarce and the few that have been conducted have typically administered smoked cannabis. Oral and vaporized cannabis products are increasing in popularity and these alternative forms of cannabis may produce stronger and/or more prolonged effects compared with smoked cannabis. However, there is presently limited data on the acute effects of co-use of alcohol and oral/vaporized cannabis, and the one study previously published on alcohol and vaporized cannabis co-use showed a significant increase in Δ9-THC and its metabolites in the combined drug condition versus cannabis alone (Hartman et al., 2015). This two-part randomized crossover clinical laboratory study will extend prior research by characterizing the acute impairing effects of alcohol and oral and vaporized high Δ9-THC cannabis, both alone and together, across multiple ecologically relevant doses. Assessments include a state-of-the-art driving simulator, a battery of field sobriety tests and cognitive and psychomotor performance tasks, and subjective drug effect instruments.

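### Post-dose blood THC exposure is a covariate in the models that test dose, so the dose terms no longer estimate the total impairment named in the primary aim

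*Protocol article*

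**What the plan says.** Section 2.14 states: "Linear mixed models will be used to test for differences across experimental conditions". The factors listed for these models are time, alcohol dose, cannabis dose and sex. The same paragraph then says that Cmax and AUC "for Δ9-THC and Δ9-THC metabolites (11-OH-Δ9-THC; Δ9-THC-COOH) will be entered as covariates". That names six measures, two summaries for each of three analytes. The text does not confine them to a secondary analysis, and it describes no model without them.

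The Introduction sets the aims. The primary one reads: "The primary aim of this two-part study is to characterize subjective, cognitive and psychomotor, and driving impairment from oral and vaporized high Δ9-THC cannabis", alone and with alcohol. The other reads: "A secondary aim is to explore possible pharmacokinetic interactions between alcohol and oral/vaporized cannabis".

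Three places describe blood exposure as a step between dosing and impairment:
- Introduction, on combined impairment in general: "which is likely driven, in part, by pharmacokinetic interactions between alcohol and Δ9-THC".
- Introduction, on the one published study of alcohol with vaporized cannabis: "the increased impairment under co-use conditions was seemingly mediated by pharmacokinetic interactions between alcohol and cannabis".
- Section 3 (Comments), on the same study, which "showed a significant increase in Δ9-THC and its metabolites in the combined drug condition versus cannabis alone".

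**The concern.** Cmax and AUC cannot be known before the session's dose is given. By Table 1, three of the seven conditions use placebo cannabis, which Section 2.4 puts below 0.01% THC. The other four give 10 or 25 mg. Exposure therefore follows the cannabis dose factor, and by the article's own account it also shifts when alcohol is added. A covariate of this kind is a consequence of treatment and a candidate mediator, not a baseline prognostic factor.

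Holding it fixed changes the question from how much impairment a condition causes to how much it causes by routes other than measured blood THC. A reader of the fitted dose terms would take them for the first and receive something closer to the second, with less precision. If the comparison of co-use with the 0.08% positive control came from such a model, the adjustment would act on one side only, because the positive control contains placebo cannabis. Section 3 proposes to draw inferences about per se limits from that comparison.

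**Working it through.** **The plan's own figure.** Section 2.14 gives 32 participants per part and power of at least 0.80, but prints no effect size, SD or correlation, so the figure cannot be reproduced. As a plausibility check, a paired contrast at two-sided 0.05 needs d = (1.960 + 0.842)/√32 = 0.495 for 80% power by the normal approximation. The noncentral t gives 0.78 at d = 0.50 and 0.81 at d = 0.52. So 32 is plausible for a within-subject d near 0.5, with no allowance for lost precision.

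**Structure.** Let m be the share of the cannabis effect that passes through measured exposure. Assume, in units of the residual SD:
- 25 mg alone has a total effect of 1.0.
- 0.05% alcohol has an effect of 0.5 (0.08% alcohol: 1.0).
- Co-use raises exposure, and the cannabis effect, 1.3-fold.

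The expected contrasts are then:
- 25 mg vs 0: 1.0 unadjusted; 1 − m adjusted.
- 25 mg + 0.05% vs 0.05% alone: 1.3 unadjusted; 1.3(1 − m) adjusted.
- 25 mg + 0.05% vs 25 mg alone: 0.5 + 0.3 = 0.8 unadjusted; 0.5 + 0.3(1 − m) adjusted.

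The first two lose the share m. The third keeps alcohol's 0.5 whatever m is.

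**Illustrative simulation.** 32 participants × 7 conditions, one score per session, a within-participant linear model, and 600 replicates per scenario. Exposure log-SD was 0.3 between and 0.4 within participants. All effect sizes, exposure SDs and values of m are assumptions, not figures from the article.

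Without the covariates, the three contrasts were about 1.0, 1.3 and 0.8. The standard error was 0.25 to 0.26, matching √(2/32) = 0.25. Power was 0.96 to 0.99, 1.00, and 0.85 to 0.90.

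With all six covariates, estimate (power):

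| m | 25 vs 0 | 25 + 0.05% vs 0.05% | 25 + 0.05% vs 25 |
|---|---|---|---|
| 100% | −0.03 (0.05) | −0.02 (0.05) | 0.49 (0.44) |
| 50% | 0.51 (0.30) | 0.63 (0.35) | 0.63 (0.62) |
| 25% | 0.74 (0.56) | 0.98 (0.68) | 0.74 (0.77) |
| 0% | 1.01 (0.84) | 1.32 (0.90) | 0.80 (0.84) |

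Adjusted standard errors were 0.35, 0.40 and 0.27. For the first contrast the variance factor is (0.35/0.25)² = 1.96, and for the second (0.40/0.25)² = 2.56.

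This inflation is present even at m = 0, because the covariate tracks dose. One covariate gave almost the same as six (0.34, 0.39 and 0.26). In a separate one-covariate run with exposure CV from 70% down to 40%, the variance factor was about 1.5 to 2.6 for the first contrast and 1.9 to 3.7 for the second.

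**The case against.** The core reading is hard to dispute, but several limits stand.

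- **Reach to the planned comparisons.** The later part of Section 2.14 compares peak change from baseline between conditions and names no covariate. A peak score has no time factor, so these comparisons need not come from the mixed model described before. The article is condensed, and a fuller plan may separate them. This stands as uncertainty, but nothing in the text exempts them.
- **Full removal of the cannabis effect.** A reader might infer that adjustment removes the whole effect. That needs m = 100%. The Introduction says that blood THC does not correlate highly with impairment, and it hedges the mediation as partial and apparent. Partial attenuation is what the article supports.
- **Co-use reported as absent.** A reader might infer that a real co-use effect would vanish. Against cannabis alone, only the pharmacokinetic-interaction part is lost. Even under full mediation the simulated contrast goes from 0.81 to 0.49, so 0.49/0.81 = 60% remains.
- **Six covariates at once.** The article lists six measures but does not say whether they enter together or one per model. The result barely depends on this.
- **Exposure near zero under placebo.** Section 2.2 admits people who use cannabis up to twice weekly and exempts THC from the urine screen, and Section 2.14 foresees raised baseline values. Collinearity with dose is strong but not exact.
- **Direction.** Shrinkage toward zero assumes no other factor that drives both exposure and impairment within a dose. Such a factor could alter the bias.

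None of this justifies the covariates in the main model. If exposure predicts impairment, they change the effect being estimated; if it does not, they cost precision.

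**Conclusion.** Wrong as written. The stated covariate rule makes the cannabis and alcohol dose terms partly direct effects at fixed blood exposure, while the primary aim is total impairment. This follows from the article's own text and does not depend on the simulation.

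The size is not known. Under the assumptions above, contrasts of cannabis with no cannabis keep roughly 1 − m of the effect, and the contrast of co-use with cannabis alone loses only its pharmacokinetic-interaction part. With no mediation at all, the standard error for 25 mg against 0 still rises by about 40% (0.25 to 0.35). The direction of the loss is well supported. The magnitudes show a range only.

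It is not established that the planned comparisons are affected, because the article does not say which model supplies them. The plan should settle that.

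**What to change.** In Section 2.14, state that the primary condition models and all planned comparisons on peak change are fitted without post-dose Cmax and AUC. Analyse Cmax and AUC as outcomes, with against without alcohol at each cannabis dose, for the secondary pharmacokinetic aim. Where they serve as predictors of impairment, place them in a separately labelled exposure-response or mediation analysis and say that its dose terms are direct effects.

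If residual cannabis from outside use is the concern, that session's pre-dose THC concentration is an optional covariate, since the session's dosing cannot affect it.

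The cost is analysis-plan wording. No data collection, visit or sample size needs to change.
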